## Abstract

**Background:**

Stroke is a leading cause of death and disability globally. India, like other low- and middle-income countries, faces rising stroke cases with significant regional variations and burden. Successful management of acute stroke requires timely recognition, quick transportation to a definitive health care facility, and specialized care for reducing mortality and morbidity. Stroke care in India is predominantly urban-oriented, private sector–dominant, with a shortage of trained or specialist personnel and limited access to infrastructure. There is a need to develop stroke care systems across various levels of health care delivery that are comprehensive and standardized for timely intervention, management, and referral.

**Objective:**

This study aims to develop and assess the effectiveness of a Comprehensive Acute Stroke Care Model (CASCADE) for managing patients who had an acute stroke in Karnataka (a state in South India) with a focus on improving survival, disability, and quality of life.

**Methods:**

This is a quasi-experimental preinterventional and postinterventional study design with the CASCADE as the intervention. This study will be conducted in 6 secondary and tertiary health care facilities, and the effectiveness of the model will be assessed on 510 patients who had a stroke for the first time (255 each in the preintervention and postintervention arms). Furthermore, the patients will be followed up on 28 days and the 3rd, 6th, and 12th month after the stroke to evaluate survival, disability, and quality of life before and after the intervention.

**Results:**

The study is funded by the SKAN Research Trust. Data collection for the preintervention arm has commenced and is currently ongoing. As of manuscript submission, approximately 100 cases have been recruited in the preintervention arm. Data analysis will begin after completion of recruitment.

**Conclusions:**

This unique, first-of-its-kind CASCADE encompasses triage algorithm, diagnosis, investigations, treatment, referral, and discharge interventions. An effective model will provide valuable insights into stroke management and is highly translatable into practice. The findings will have significant implications for policymaking and stroke-related public health programming in India.

**Trial Registration:**

Clinical Trials Registry-India CTRI/2023/04/051370; https://tinyurl.com/44wwehpr

**International Registered Report Identifier (IRRID):**

DERR1-10.2196/93984

## Introduction

### Background

Globally, stroke is the leading cause of disability and the second leading cause of death [1]. In the last two decades, the lifetime risk of stroke has increased by 50%, with 1 in 4 people estimated to have a stroke in their lifetime [2]. Annually, 6.5 million people die from stroke, constituting approximately 6% of deaths among those aged 15 to 45 years-. Over 143 million healthy life years are lost annually, with 15% lost among those aged 15 to 45 years. India, like other low- and middle-income countries, is experiencing a stroke epidemic. It is the fourth leading cause of death and fifth leading cause of disability in India [3]. Karnataka, a southern Indian state, ranks ninth among all states in India in incidence of stroke. With 109 new patients who had a stroke for every 1,00,000 of its population in 2019, Karnataka had higher incidence of stroke than the national average [4].

Appropriate, timely, and efficient stroke management is crucial for improved outcomes, as standardized care systems have shown to reduce mortality and enhance functional outcomes in acute stroke cases. Effective management requires prompt recognition, rapid transportation to health care facilities, and specialized care to minimize deaths and disabilities [5]. In India, stroke care is mostly urban centric and private sector driven, with shortages of trained specialists and limited access to imaging and diagnostics [6,7]. Even medical college hospitals face a shortage of neurologists, highlighting the need for alternative care models [8]. There is a critical need to develop comprehensive, standardized stroke care systems across different levels of health care delivery for timely intervention, management, and referrals [5,9-11]. While some care models exist, especially in hospital settings, community-based models tailored for India are rare [12].

### Aim

This quasi-experimental study aims to develop and assess the effectiveness of a Comprehensive Acute Stroke Care Model (CASCADE) in Karnataka, India, on improvement of preparedness, pathways to care, and management practices related to stroke in different health care settings and improvement in survival, disability, and quality of life (QoL) of patients who had an acute stroke.

## Methods

### Study Design

We plan to conduct a quasi-experimental preinterventional and postinterventional study.

### Study Setting

The health care facilities comprise 1 neurospecialty hospital (a caseload of approximately 300 cases per month) and 1 medical college hospital (a caseload of approximately 50 cases per month) at the tertiary level and 1 district hospital (a caseload of approximately 30 cases per month), 1 medical college hospital (a caseload of approximately 50 cases per month), and 2 government hospitals (a caseload of approximately 50 and 30 cases per month) at the secondary level in Karnataka.

### Characteristics of the Study Units

The study unit consists of health care facilities including health care personnel and patients who had a stroke. Health care facilities and their personnel will be the unit of study for stroke care preparedness, while all patients who had a stroke for the first time (both ischemic and hemorrhagic) attending the emergency rooms of these hospitals and/or admitted within the hospital during a 1-year period (or until the requisite sample size is obtained, whichever is earlier) will be the unit of study to assess CASCADE effectiveness before and after the intervention.

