#### The CASCADE: Development, Implementation, and Assessment of Effectiveness

The intervention is the CASCADE, which will be developed through a process of observation and expert consultation. The CASCADE intervention is a structured, multicomponent health care facility–based intervention tailored to each participating facility based on findings from the hospital preparedness assessment and gap analysis. While site-specific modifications may differ according to identified gaps, the overall intervention framework will remain uniform across all participating health care facilities. The detailed intervention package will be developed using evidence generated from the preintervention stroke data, hospital preparedness assessments, Indian stroke management guidelines, and recommendations from an expert panel that will validate and standardize the protocols and algorithms across different levels of care. The proposed CASCADE will include procedures and standards for screening, triaging, and management of stroke cases at different levels of health care, algorithm-driven management, and referral of stroke cases. The effectiveness or outcomes of the CASCADE being assessed are stroke survival, disability, and QoL over a period of 1 year after the stroke.

Once developed, the CASCADE will be implemented across study units. Health care facilities will be informed about their preparedness, management practices, and needed improvements based on preimplementation scores and indicators. Suggested modifications and personnel training will be provided. Training attendance, supportive supervision, and adherence to standardized protocols and algorithms will additionally be monitored during implementation. Implementation fidelity will be assessed using both facility-level and patient-level indicators. Preintervention and postintervention hospital preparedness assessments using standardized tools will evaluate changes in infrastructure, service availability, referral mechanisms, and stroke preparedness processes. The same indicators and scoring system will be used after the intervention to compare and estimate effectiveness of the CASCADE on outcomes of stroke care in the study unit. Figure 1 provides a schematic representation of development and implementation of the CASCADE.

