### Data Collection

#### Patient-Related Information

Data collection will be conducted through face-to-face or telephonic interviews with patients who had a stroke or their caregivers (if patients are aphasic). Acute stroke cases will be assessed through an in-person interview at the time of presentation at hospital (recruitment), during the hospital stay, and at discharge. Clinical and laboratory records will be reviewed to collect data on stroke type, clinical presentation, investigations, patient and sample journeys, disability assessment, and treatment outcomes (death, disability, and QoL). Telephonic interviews are planned for follow-ups if travel is not feasible, with medical records sourced via email or other personalized social media platforms. This is being done to improve participant retention in the study.

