### Statistical Analysis

The respondents in the preimplementation phase of the CASCADE are considered group 1 and those in the postimplementation phase as group 2. The primary outcome for CASCADE effectiveness includes improved hospital preparedness and improved patient treatment outcomes (death, disability, and QoL). The timing and sequence of implementation at each site will be documented in case of minor variations in the timing of intervention implementation across participating sites due to administrative or operational factors beyond the control of the investigators. These factors will be incorporated into the statistical analysis plan. Site-level and time-related variations will be adjusted for during analysis to account for potential differences in implementation timing across hospitals. We hypothesize that the treatment outcomes in group 2 will be better than those in group 1. The Kaplan-Meier method will be used for estimating the survival functions of the two groups at follow-up. The log-rank test will be used to compare the survival distributions between the two groups for each time point. Finally, the Cox proportional hazards regression analysis will be performed at each of the 4 time points separately in which the grouping variable is the intervention (CASCADE) in addition to potential confounders. Relevant patient-level covariates, including stroke severity, National Institutes of Health Stroke Scale score, timing of presentation, referral pathway, and other clinical characteristics, will be considered as potential confounders in adjusted analyses. The QoL before and after the implementation of the CASCADE will be compared using an independent sample 1-tailed *t* test or the Mann-Whitney *U* test depending on the normality assumption. Linear mixed models will be used in which QoL is the dependent variable and the CASCADE is the main independent variable. In the model, the group and the 4 time points are fixed factors and participants are considered as random. The modified Rankin Scale (mRS) scores before and after implementation of the CASCADE will be compared using the Mann-Whitney *U* test at each time point after adjusting for multiple comparisons using the Bonferroni method. Survival rate by different categories of stroke (hemorrhagic and ischemic) and by different severities of stroke (Glasgow Coma Scale and mRS based) will be used for evaluation of effectiveness of the model.

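### CASCADE changes how strokes are detected and classified in phase 2 only, and the plan does not keep a shift in who is counted, or under which stroke type, apart from a survival benefit

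*Protocol article*

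**What the plan says.** - **Who enters.** Characteristics of the Study Units takes "all patients who had a stroke for the first time (both ischemic and hemorrhagic) attending the emergency rooms of these hospitals" or admitted there, before and after the intervention.
- **What CASCADE changes.** The section on its development and implementation lists "procedures and standards for screening, triaging, and management of stroke cases at different levels of health care", together with referral. The abstract's Conclusions say that the model "encompasses triage algorithm, diagnosis, investigations, treatment, referral, and discharge interventions". All of this starts after phase 1.
- **Where type comes from.** Under Patient-Related Information: "Clinical and laboratory records will be reviewed to collect data on stroke type, clinical presentation, investigations".
- **How it is used.** Statistical Analysis compares the phases with Kaplan-Meier curves and an unadjusted log-rank test, then Cox models. NIHSS, severity, timing and referral pathway are to be considered as confounders. "Survival rate by different categories of stroke (hemorrhagic and ischemic) and by different severities of stroke" is also to serve in evaluating effectiveness, and the section aims for better survival at every severity level.
- **How shifts are to be read.** The Discussion (Principal Findings) names case mix, referral patterns and diagnostics among the influences on survival. It says several such changes may belong to the intervention exposure and not merely be a bias. Only factors not directly related to the intervention are promised documentation and consideration there.

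**The concern.** In a before-after comparison, the set of patients counted and the labels they carry need to mean the same thing in both periods. Here the intervention acts on both. If trained staff recognise milder strokes that would have passed unnoticed in phase 1, those patients enter the phase 2 denominator with good survival and the 28-day comparison improves. If better work-up changes which patients are called ischaemic or haemorrhagic, both strata can improve while total deaths stay the same.

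This differs from ordinary drift in case mix because CASCADE itself would cause it. The Discussion's division makes it worse. A detection shift caused by CASCADE is directly related to the intervention, so it falls on the side that may be read as exposure and not on the side to be handled as bias. At stake are the primary 28-day survival comparison (through detection) and the type subgroups (through classification).

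**Working it through.** **1. The plan's own figure.** From Sample Size: 28-day survival 42% before and 57% after, 5% significance, 90% power, 10% dropout.
- Hazard ratio: ln(0.57)/ln(0.42) = 0.648 (stated 0.65).
- Freedman events: (1.960 + 1.282)² × [(1 + 0.648)/(1 − 0.648)]², which gives 231 (stated 232).
- Total: 2 × 231/(2 − 0.42 − 0.57) = 457.4 (stated 458). With dropout: 458/0.90 = 509 (stated 510).

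The sample size reproduces with a two-sided test and is not in dispute. It leaves 458/2 = 229 evaluable patients per phase.

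**2. Detection shift with unchanged prognosis.** Let f be the share of phase 2 patients who would not have been recognised in phase 1, and s their 28-day survival. The documents give neither, so both are assumptions. Apparent phase 2 survival is 0.42(1 − f) + s·f.

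The share that reproduces the whole planned gain is f = (0.57 − 0.42)/(s − 0.42). The last two columns give the chance that an unadjusted two-sided 5% comparison favours CASCADE (two-proportion normal approximation, 229 per phase, standing in for the log-rank test). The nominal chance in that direction is 2.5%.

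| Assumed s | f that gives 57% | Favours CASCADE, f = 10% | Favours CASCADE, f = 20% |
|---|---|---|---|
| 0.80 | 39.5% | 13% | 37% |
| 0.90 | 31.2% | 18% | 54% |
| 0.95 | 28.3% | 21% | 62% |
| 1.00 | 25.9% | 24% | 70% |

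At s = 0.90:
- f = 10%: 0.9 × 0.42 + 0.1 × 0.90 = 46.8%, apparent hazard ratio 0.88.
- f = 20%: 0.8 × 0.42 + 0.2 × 0.90 = 51.6%, apparent hazard ratio 0.76.

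**3. Direction.** The shift is favourable only if s exceeds 0.42. With an assumed s = 0.20 and f = 10%, apparent survival is 0.9 × 0.42 + 0.1 × 0.20 = 39.8%, below baseline.

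**4. Classification shift (invented counts, for illustration).** Take 100 patients with 42 survivors: 38/80 = 47.5% in the ischaemic stratum and 4/20 = 20.0% in the haemorrhagic stratum. Relabel 10 patients, 3 of them survivors, from ischaemic to haemorrhagic. The strata become 35/70 = 50.0% and 7/30 = 23.3%. Both rise, because the moved patients' 30% survival lies between the two original rates. Overall survival is 42/100 both times, so this mechanism cannot touch the primary outcome.

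**The case against.** Much of the other side's case stands.

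- **Entry by hospital diagnosis is not stated.** A reader might infer that the hospital's own diagnosis decides who is enrolled. The article does not say who confirms a stroke or by what criteria, and a condensed article may leave that to the full protocol. Only the record source for type and clinical presentation is explicit.
- **Under-imaging at these sites is not stated.** The Background describes shortages of specialists and imaging in India generally, not at the six study hospitals. Nothing says that haemorrhages there go unimaged.
- **Adjustment is planned, and NIHSS is not said to come from records.** The record-review list does not name NIHSS. Patients are seen in person at presentation, data collectors are trained at each cycle, and 5% of data collection is repeated. If NIHSS is scored at arrival in the same way in both phases, extra mild strokes are largely measurable case mix. The claim that adjustment fails is therefore not supported. What remains is that covariates are only to be considered, the log-rank test uses none, and severity adjustment does not correct a changed type label.
- **The enrolment quota limits the size.** Half the patients come from the neurospecialty hospital, where missed strokes are less plausible. With no shift there, an overall share of 10%, 20% or 31% means 20%, 40% or 62% at the other sites. A share large enough to produce the full planned gain is hard to believe; a smaller one is not.
- **Some of this is acknowledged.** Investigations are recorded in both phases, the Discussion names case mix and diagnostics, and Limitations concedes residual confounding. But Limitations attributes it to unknown confounders, and this source is known in advance.

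**Conclusion.** The concern holds in a limited form. Detection and classification can shift with CASCADE, the unadjusted comparison and the type subgroups are exposed to that, and the Discussion allows such a shift to be read partly as benefit. Survival can rise for this reason; nothing shows that it will, and better recognition of severe strokes would lower it.

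The size cannot be derived from the documents. At an assumed 80-100% survival, newly recognised cases would have to be about 26-40% of phase 2 to produce the entire planned effect. A 10-20% share at 90% survival already lifts the chance of a favourable unadjusted result to about 18-54%, against 2.5%. These figures assume unchanged prognosis and no adjustment; uniform arrival severity with adjustment would reduce them.

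A reader might also infer that relabelling can turn the primary 28-day comparison favourable. It cannot: it moves patients between strata and leaves overall survival as it was.

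**What to change.** 1. In Statistical Analysis, base the effectiveness conclusion on the comparison adjusted for arrival NIHSS, and treat the unadjusted log-rank test as descriptive. Add a sensitivity analysis restricted to patients above a fixed arrival NIHSS, with the cut-off set before phase 2 data are seen.
2. Report stroke type as imaging-confirmed ischaemic, imaging-confirmed haemorrhagic or not imaged, using the investigations already recorded. Draw no effectiveness claim from the type subgroups if the not-imaged share differs between phases.
3. Screen the same emergency and admission registers in both phases, log suspected strokes, and report the counts by phase. A rise in recognised mild cases then becomes visible.
4. Amend the Discussion so that changes in who is detected, or how they are classified, are treated as bias and not as intervention benefit.

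The cost is protocol wording, some added logging and a small amount of analysis. The log cannot be fully rebuilt for phase 1 patients already enrolled (98 of 255 by February 2026). Phase 1 recruitment is due to end in June 2026, so the log is worth most if it starts at once.

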### Description of Materials

All aspects of stroke care from the time of onset to discharge and after discharge (for 1 year), namely preparedness, management, pathways to care, and the CASCADE, shall be assessed using semistructured, partially open-ended schedules (Table 1).

**Table 1 table1:** Proposed content for each data collection time point in the schedule—Comprehensive Acute Stroke Care Model (CASCADE).

Name of the schedule	Contents or scale used	Study units	Time points of data collection
Preparedness schedule for a health care facility	Information related to all aspects of preparedness, including personnel, infrastructure, guidelines, training, and management related to stroke	Health care facilities identified for the CASCADE	Once in the preimplementation phase and once in the postimplementation phase
Baseline schedule for collecting basic information of patients who had a stroke to understand the existing management practices during the preimplementation phase and to assess the effectiveness of the developed CASCADE in the postimplementation phase	Detailed information on sociodemographic characteristics, risk factors, their date of onset or diagnosis, duration, dose or amount of risk factor as appropriate (eg, average number of cigarettes smoked per day and alcohol consumed per day), current status, and dependence information (as appropriate)	All patients who report to the hospitals enrolled for assessment of the CASCADE	As and when individuals report to study hospitals with a stroke during the study period (both preintervention and postintervention of the CASCADE)
Management schedule to understand the management of stroke cases	Includes case record forms with information related to history, clinical information, laboratory investigations conducted, management procedures performed, and drugs prescribed	All patients who report to the hospitals enrolled for assessment of the CASCADE	As and when individuals report to study hospitals with a stroke during the study period, preintervention and postintervention of the CASCADE
Pathways to care schedule to collect information on stroke outcome	Includes information related to different treatments and care sought in different places or systems of medicine before reporting to the study hospitals	All patients who report to the hospitals enrolled for assessment of the CASCADE	As and when individuals report to study hospitals with stroke during the study period, preintervention and postintervention of the CASCADE
Outcome schedule	Information related to survival, and disability: Modified Rankin Scale and Stroke-Specific Quality of Life Scale	All patients who report to the hospitals enrolled for assessment of the CASCADE	As and when individuals report to study hospitals with a stroke during the study period and subsequent follow-ups (28 days, 3 months, 6 months, and 12 months after the stroke)
CASCADE schedule	Information related to the standardized CASCADE. This shall contain treatment and management algorithms for stroke care at different levels of health care. This will be developed using information from the preparedness, management, pathways to care, and outcome schedules followed by validation by an expert advisory group. This will be a synthesis of data of all patients who report to the hospitals enrolled for assessment of the CASCADE in the preintervention phase.	All patients who had a stroke within the study hospitals who are eligible for assessment in both the preintervention and postintervention period of the study	As and when individuals report to study hospitals with stroke during the study period preintervention and postintervention of the CASCADE

